## Methods/design

### Study design

The study is a randomised controlled trial comparing speech and language treatment as usual with a music-assisted programme for learning language. The online version of the free open-source Python programme, MinimPy [18], will be used by the PI (FL, who will have no prior interactions with the participants) to assign the participants randomly to either the music-assisted (MAP) intervention or treatment as usual (TAU) group using minimisation randomisation. This method prevents selection bias and minimises the imbalance in prognostic factors of participants between treatment groups [19]. Gender, developmental stage (IQ ≥ 70 or 50–69) and echolalia (present or absent, as reported by the parents) will be used to balance participants between groups.

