### Participants

Thirty children with ASD will be recruited. This sample size was determined partly based on sample sizes of previous studies that used a similar design, ranging from six [20], twelve [21], 23 [22], to 50 divided across three groups (18, 18, 14 in each group) [23]. In addition, for a small randomised controlled feasibility trial like the current one, the sample size can be established according to the precision required for the critical objectives (e.g., estimation of recruitment rate), rather than through power analysis [24]. With a sample size of 30, we will be able to estimate a drop-out rate of 20% to within a 95% confidence interval of +/− 14% [25]. Finally, it has been recommended that pilot studies should include 12 per group [26] or 30 or more participants [27, 28] in order to estimate the means and standard deviations of the outcome measures, as well as to facilitate a sample size calculation for the full trial. Thus, a sample size of 30 is deemed adequate for the current study.

Participants will be screened for autism spectrum disorder using the Social Responsiveness Scale-2 (SRS-2) [29]. They will be between 24 and 60 months old, with little or no spoken language, defined operationally as fewer than 20 functional words [30]. Adapting Dawson et al. (2010: e18) [31], the following will be the exclusion criteria:A neurodevelopmental disorder of known aetiology (e.g., fragile X syndrome);Significant hearing or motor impairment;Major physical problems such as a chronic serious health condition;Seizures at time of entry;History of a serious head injury and/or neurologic disease;IQ below 50 as measured by the Vineland Adaptive Behavior Scales – Third Edition [32]; andNot meeting the cut-off score for ASD on the SRS-2.

The participants will be recruited from special education preschool provision, National Health Service (NHS—state funded), voluntary groups, social media and privately funded clinics in the UK. The parents of potential participants will be approached by letter or email initially and asked to complete an online questionnaire assessing the child’s eligibility and asking for consent to take part in the trial. All data will be held on a secure password-protected database accessible only to the research team.

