### Baseline and outcome measures

Outcome measures will be collected at four time points: pre-, mid-, post-intervention and 3-month follow-up (see Fig. 1 and the SPIRIT checklist [35] in Supplementary Material). The measures will be administered by the research therapist using telecommunication methods including video conferencing technology to direct the caregiver to manipulate materials appropriately. The measures can be successfully administered with non-verbal and minimally verbal children and can ultimately be easily integrated in clinical and research settings. They will be scored by the research therapist and checked by a research assistant who will be blind to allocation. However, the parent administering the measures will also have been using the intervention methods with their children and thus there is very limited blinding possible in this trial. Demographic details and a medical history will be obtained at intake to the trial. Given the small size of this randomised controlled feasibility trial, there is no need to define primary versus secondary outcomes [24]. Thus, the following outcome measures are listed with no particular order.One key outcome is the expressive (picture naming) and receptive (pointing to correct picture) tasks to assess the production and comprehension of the 36 target words at baseline, post-intervention, and 3-month follow-up. A preliminary list of 36 target words has been drawn up (Table 1), but the protocol includes 35 backup words (Table 2) and allows substitutions of up to 10 words if required by the prior skills of the child;Social Responsiveness Scale-2 (SRS-2) - Participants’ ASD symptomatology will be assessed using the Social Responsiveness Scale-2 [29]. The SRS-2 is a questionnaire that uses a scale of 1–4 (1 = not true, 4 = almost always true) to rate items, with higher scores indicating greater impairment [36, 37]. A designated raw score cutoff value of 70 is considered to have a sensitivity of 0.78 and specificity of 0.94 for ASD [38]. Raw total scores are converted to gender-normed T scores, with a T score of 75 indicating severe impairment. Item-level and full scale (both raw and T scores) scores were included in the analyses.Receptive and expressive language skills will be measured using the Expressive One-Word Picture Vocabulary Test–4 (EOWPVT-4) [39] and the Receptive One-Word Picture Vocabulary Test-4 (ROWPVT-4) [40], and by MacArthur Bates Communicative Development Inventories (CDI): Words and Gestures Forms [41]. The EOWPVT-4 and ROWPVT-4 tests give raw score which can be used to determine standard score, age-equivalent score and percentile rank. The tests are appropriate for use with typical and atypical populations, including those with learning difficulties. The CDI has high parent-teacher agreement for children with ASD (intraclass correlation 95% CI estimates 0.77 to 0.93) [42].The child’s social communication will be evaluated during a 10-min video recorded free play session between the child and their parent. Social communication will be measured using the Parent-Child Dyadic Interaction Measure which has good intrarater (*κ* = .81) and good interrater reliability (*κ* = .80) [43].Functional language will also be evaluated during the 10-min video recorded free play session between the child and their parent. Casenhiser et al.’s (2015) [44] approach to coding language functions will be used which shows good internal consistency (Cronbach’s *α* range 0.830–0.836) as is the validity compared with other measures of communication level. A week-long language diary to be filled out by parents at pre-, mid-, post-intervention and 3-month follow-up will also help determine the child’s progress on language development.Communication, daily living skills, socialisation and maladaptive behaviour will be measured using the comprehensive parent/carer form of Vineland Adaptive Behavior Scales – Third Edition (VABS-3) [32], to be filled out by parents/caregivers. The VABS-3 has high internal consistency (Cronbach’s *α* range 0.86–0.97), good test-retest reliability (corrected *r* values range 0.62–0.92), and good inter-rater reliability (range 0.61 to 0.87). Data show that it has criterion validity for identifying those with intellectual disability.

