We will record and report the participant flow according to CONSORT guideline and produce a CONSORT flowchart [45, 46]. As a feasibility trial, we will report recruitment and retention figures for both MAP and TAU together with reasons for loss of participants. The trial management will consider any adverse effects and use that information to continue or halt the trial. In addition, we will discontinue the trial at the request of the caregivers, ongoing distress on the part of either the child or the caregiver, and if the caregiver takes up an additional language intervention during the trial. We expect to analyse recruitment and retention data using descriptive statistics involving both intention to treat and actual completed participant data. Recruitment and retention will be encouraged by payment of £202.50 ($283.00) to participants families for completing the research. The amount of the missing data will be recorded in order to assess the feasibility of using each measure. An important part of the feasibility is the extent to which it is possible to conduct two training sessions per week and still maximise the homework practice. We will therefore review the uptake/usage pattern of all MAP parent-child dyads to establish the feasibility of delivering 36 sessions over 18 weeks. For the outcome measures, descriptive data will include means and standard deviations for continuous normal data, and medians and inter-quartile ranges for continuous non-normal or discrete data. Standard errors/confidence intervals will also be calculated for continuous normal data or percentages. Statistical analyses will be performed in R [47]. The results from these analyses will provide data for effect size estimation. Together with the trial parameter data (i.e., recruitment, retention, follow-up and completion rate), these data will be used to determine the size of sample necessary to carry out a fully powered randomised controlled trial comparing MAP with SCIP. A preliminary categorical analysis of words learnt may be used to inform the selection of future vocabulary items for a subsequent trial. The numerical data will be analysed blind to allocation. The blinding will be carried out once the data are collected by generating a new series of participant codes, removing data that could lead to identification (TW) and then be analysed by the PI (FL). Anonymised behavioural data and statistical analysis codes will be made available following open access guidelines. The qualitative interview data will be transcribed and analysed using the thematic analysis framework [48] and Nvivo 12 [49].

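### The effect-size and sample-size inputs for the full trial come from descriptive summaries that make no named use of the baseline scores; a baseline-adjusted difference and the baseline-outcome correlation would be a low-cost gain

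*Protocol article*

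**What the plan says.** In the Protocol article, the second main objective (Background) is to supply the parameters for the sample size and effect size of a later full trial.

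- **Outcome analysis (Data handling and analysis plan).** For the outcome measures, "descriptive data will include means and standard deviations for continuous normal data", with medians and interquartile ranges for other data, and standard errors or confidence intervals. Then: "The results from these analyses will provide data for effect size estimation". Together with recruitment and retention figures, these data are to determine the size of the full trial.
- **Baseline scores (Baseline and outcome measures).** "Outcome measures will be collected at four time points: pre-, mid-, post-intervention and 3-month follow-up". The target-word tasks also have a baseline: they assess production and "comprehension of the 36 target words at baseline, post-intervention, and 3-month follow-up".
- **Allocation (Study design).** "Gender, developmental stage (IQ ≥ 70 or 50–69) and echolalia (present or absent, as reported by the parents) will be used to balance participants between" the two arms.
- **Sample size (Participants).** "Thirty children with ASD will be recruited". The justification is that "the sample size can be established according to the precision required for the critical objectives (e.g., estimation of recruitment rate), rather than through power analysis".

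No model, covariate, residual SD or baseline-outcome correlation is named. The article does not call the effect size unadjusted either, and it does not state how the full trial will be analysed.

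**The concern.** The named route from data to effect size to sample size consists of descriptive summaries. If it is followed as written, two things are lost.

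1. **Precision.** With about 15 children per arm, a chance difference at baseline carries into a simple comparison of post-intervention means. Conditioning on each child's own baseline score removes the part that baseline predicts.
2. **A planning parameter.** A full trial analysed with baseline adjustment is sized on the residual SD, or equivalently on the raw SD together with the baseline-outcome correlation. Separate means and SDs at each visit give neither.

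The practical stake is a full trial larger than necessary, in a population whose recruitment the article itself treats as an open feasibility question.

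**Working it through.** **The plan's own figure.** "With a sample size of 30, we will be able to estimate a drop-out rate of 20% to within a 95% confidence interval of +/− 14"%. Check: 1.96 × √(0.2 × 0.8 / 30) = 0.143, so it reproduces.

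**Inputs from the article.** N = 30. A 20% drop-out leaves 30 × 0.8 = 24 completers.

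**Assumptions, not in the article.** Equal allocation (15 per arm, 12 after drop-out); baseline-outcome correlation ρ = 0.3, 0.5 or 0.7; for the full trial, an effect d = 0.5 SD, two-sided α = 0.05 and 80% power.

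**Precision within this trial.** In SD units, the unadjusted SE of the difference is √(2/m), with m per arm. With one baseline covariate it is multiplied by √(1 − ρ²) × √(1 + 1/(N − 4)); the second factor is the price of estimating the slope.

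| ρ | SE, 12 per arm | Reduction | SE, 15 per arm | Reduction |
|---|---|---|---|---|
| unadjusted | 0.408 | – | 0.365 | – |
| 0.3 | 0.399 | 2% | 0.355 | 3% |
| 0.5 | 0.362 | 11% | 0.322 | 12% |
| 0.7 | 0.299 | 27% | 0.266 | 27% |

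At ρ = 0.5 and 12 per arm, the 95% half-width goes from 1.96 × 0.408 = 0.80 SD to 1.96 × 0.362 = 0.71 SD. A simulation of 20,000 trials with 12 per arm agrees (0.407 to 0.361). At ρ = 0, adjustment costs a little (0.409 to 0.418).

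**Size of the full trial.** Per arm, n = 2 × (1.960 + 0.842)² × (1 − ρ²) / d², rounded up. At d = 0.5 the raw SD gives 62.8, so 63. The other columns give power at d = 0.5 when the sizing SD and the analysis do not match.

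| ρ | n per arm, adjusted SD | Power with 63 per arm, adjusted analysis | Power with adjusted-SD n, unadjusted analysis |
|---|---|---|---|
| 0.3 | 58 | 84% | 77% |
| 0.5 | 48 | 90% | 69% |
| 0.7 | 33 | 98% | 53% |

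At ρ = 0.5 the difference is 63 − 48 = 15 per arm, or 30 children. The last two columns show that neither SD is right in itself: the correct one is that of the analysis the full trial will use.

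**Adding the three balancing factors.** With k covariates, the variance relative to the unadjusted difference is (1 − ρ²)(n − 3)/(n − 3 − k). At n = 24:

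| ρ | Baseline only (k = 1) | Baseline plus three factors (k = 4) |
|---|---|---|
| 0.3 | 0.96 | 1.12 |
| 0.5 | 0.79 | 0.93 |
| 0.7 | 0.54 | 0.63 |

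The last column supposes that the factors predict nothing beyond baseline. Under that assumption the larger model is worse than no adjustment at ρ = 0.3. What the factors would really contribute cannot be computed from the article.

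**What adjustment does not cure.** In the simulation with true d = 0.5, ρ = 0.5 and 12 per arm, the full-trial n per arm planned from the observed effect (where positive) has an interquartile range of 22 to 147 unadjusted and 18 to 112 adjusted. The ratio of upper to lower quartile is 147/22 = 6.7 against 112/18 = 6.2, so the relative spread hardly moves. The correlation is imprecise too. With 24 children and an observed within-arm ρ of 0.5, the Fisher interval is tanh(0.549 ± 1.96/√20), or 0.11 to 0.76.

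**The case against.** The strongest objection is that this rests largely on silence. The article says what the descriptive data will include, not what they are limited to. Covariates are ordinary content for a separate analysis plan, which may exist. A reader might infer that the investigators have chosen an unadjusted analysis; the text does not say so. What remains is narrower: the article does state which results feed the effect size and sample size, and the only ones it names are descriptive.

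A reader might also infer that the full trial will be wrongly sized. That is not supported. The raw SD is the right input for an unadjusted full trial, and for an adjusted one it errs towards too many children, not too few. Replacing the raw SD outright by the residual SD could do harm, since it would underpower a full trial analysed without adjustment.

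A third tempting step is that, because three factors were balanced, all three should enter the main model. At this sample size that can lose precision.

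Three further points stand in part:

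- Children enter with fewer than 20 functional words, and up to 10 known target words can be swapped out. Baseline expressive scores may therefore sit near the floor and predict little. The expressive vocabulary test is open to the same doubt.
- Sample size was justified by feasibility precision, so descriptive reporting fits the design.
- Baseline and follow-up scores are kept per child and the anonymised data will be shared, so the correlation could still be computed later. That limits the harm, but sizing the full trial is a declared aim and this parameter serves it.

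**Conclusion.** The point holds as a low-cost efficiency improvement, not as an error in the plan. The named inputs to the effect size and to the full trial's sample size make no use of the baseline scores. An adjusted between-arm estimate would be appreciably more precise where the correlation is moderate or high: the SE falls by about 11–12% at 0.5 and 27% at 0.7, but only 2–3% at 0.3. Sizing from the raw SD may oversize a full trial that is later analysed with baseline adjustment, by 5, 15 or 30 children per arm (63 against 58, 48 or 33).

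These figures rest on an assumed correlation, an assumed effect of 0.5 SD, 80% power, equal arms and an adjusted full-trial analysis, none of which the article gives. Whether the full trial would be mis-sized at all cannot be settled from the document. An effect estimated from 12 to 15 children per arm remains highly uncertain with or without adjustment.

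**What to change.** In Data handling and analysis plan, keep the descriptive tables and add a short paragraph:

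- For each continuous outcome with a usable baseline, report the between-arm difference with its 95% confidence interval from a linear model on arm and baseline score, at post-intervention and separately at 3 months.
- For target-word naming, where known words are replaced, use another baseline language measure as the covariate, such as the CDI.
- Report the raw SD, the residual SD and the baseline-outcome correlation with its confidence interval.
- State that the SD used to size the full trial will match that trial's planned analysis: residual SD if baseline-adjusted, raw SD if not.
- Treat a model that also includes gender, developmental stage and echolalia as a sensitivity analysis only.

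If a separate analysis plan already specifies adjustment, one sentence pointing to it is enough. The cost is one paragraph and a few lines of R on scores already collected, with no new data, visits or children. The baseline covariate uses one degree of freedom, which matters slightly only where baseline predicts almost nothing.

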**Discussion:**

This feasibility randomised controlled trial will establish the acceptability and estimate the power of the MAP intervention to improve early word learning in children with ASD. In the longer term, this research will help us develop an app for parents or carers of children with ASD to design their own songs and implement their own individualised MAP.

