This evidence supports the use of music as a mechanism for intervention and a review of music therapy for individuals with ASD reported that music-based intervention may improve interaction and social communication, including verbal communication [5]. However, the evidence was limited by the small sample sizes of the included studies. More recently, a review of music-based intervention, including for children with ASD, found most studies measured social communication rather than language outcomes [17]. Where language was a target of intervention, evidence was positive but not conclusive. Thus, basic science and evidence from music-based intervention provide a rationale for the aim of this research to use the musical skills and interests of children with ASD to improve learning of single words.

The main objectives of this trial are therefore (1) to determine the feasibility of carrying out a randomised controlled trial of music-assisted programmes delivered remotely due to the COVID-19 pandemic to preschool children with minimal or no spoken language skills, (2) to provide essential parameter data to calculate the sample size and the effect size estimates of a future full-scale trial, (3) to optimise the music-assisted intervention design through a post-intervention interview study with parents, and (4) to pilot and refine an app available on smartphones for supporting and recording homework sessions alongside the intervention.

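### The effect size estimated from 30 children is to help set the full-trial sample size, with no independently justified target difference, and it is too imprecise for that

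*Protocol article*

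**What the plan says.** Three places in the protocol article bear on the use of the effect size.

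- Background, second objective: the trial is "to provide essential parameter data to calculate the sample size and the effect size estimates of a future full-scale trial".
- Data handling and analysis plan: outcomes are summarised by means and SDs or medians and inter-quartile ranges, with standard errors or confidence intervals. Then "The results from these analyses will provide data for effect size estimation". The next sentence says that these data, together with recruitment, retention, follow-up and completion rates, will determine the sample size of the full comparison of MAP with SCIP.
- Abstract, Discussion: the trial will "estimate the power of the MAP intervention to improve early word learning in children with ASD".

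Two further places set the context.

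- Participants: "Thirty children with ASD will be recruited". The justification cites similar small studies, then precision: a 20% drop-out rate can be estimated "to within a 95% confidence interval of" ±14%. It then cites rules of 12 per group or 30 in total for estimating outcome means and SDs and for helping to size a full trial. It gives no precision for the difference between arms.
- Baseline and outcome measures: "there is no need to define primary versus secondary outcomes". The target-word naming and pointing tasks are nevertheless introduced as one key outcome.

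**The concern.** A full-trial sample size needs two kinds of input. Nuisance quantities (SD, baseline-to-post correlation, retention) can reasonably come from a feasibility trial. The target difference is a judgement about what gain is worth detecting, and a small trial cannot supply it. The article describes the effect size as something this trial will deliver, feeds it into the sizing, and mentions no other source for the target difference.

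The required size varies as 1/d², so error in d is greatly magnified. A chance high estimate gives a full trial too small to detect the real effect. A chance low or negative one makes the full trial look unaffordable or pointless. Supplying sizing inputs is one of four stated objectives, so the problem affects a main product of the trial, although the harm would fall on the next one.

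**Working it through.** **Inputs from the article.** 30 children; two arms by minimisation; 20% drop-out, used there to illustrate precision; 95% confidence.

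**Assumptions.** Allocation 1:1 (the ratio is not stated); unadjusted comparison of two means; normal outcome with SD 1; two-sided 5% test and 80% power in the full trial. Two cases are shown: all 30 analysed (15 per arm), and 30 × 0.80 = 24 analysed (12 per arm).

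**1. The article's own figure.** 1.96 × √(0.2 × 0.8 / 30) = 0.143. The stated ±14% is reproduced.

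**2. The same precision calculation for the effect size.** Near d = 0 the half-width is 1.96 × √(2/n), with n per arm.

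- n = 15: 1.96 × √(2/15) = 0.72
- n = 12: 1.96 × √(2/12) = 0.80

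For an observed d of 0.5, exact noncentral-t limits are −0.23 to 1.22 (n = 15) and −0.32 to 1.31 (n = 12).

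**3. What that interval means for the full trial.** N per arm = 2 × (1.96 + 0.8416)² / d² = 15.70 / d².

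| d | N per arm |
|---|---|
| 0.2 | 393 |
| 0.3 | 175 |
| 0.5 | 63 |
| 0.8 | 25 |
| 1.3 | 10 |

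An observed d of 0.5 is thus compatible with about 10 per arm at the upper limit (12 per arm analysed) and with no finite size at the lower, which is below zero.

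**4. Behaviour if the point estimate is plugged in, true d = 0.5.** True power of the resulting trial is Φ(0.5 × √(N/2) − 1.96). It is below 50% when N ≤ 30, which happens when the observed d is at least 2.80 × √(2/30) = 0.72. From the noncentral t distribution of the observed d:

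| | 12 per arm | 15 per arm |
|---|---|---|
| Observed d ≤ 0 | 11% | 9% |
| Derived N per arm, 10th–90th percentile, given d > 0 | 13–641 | 15–597 |
| Derived N per arm, quartiles, given d > 0 | 23, 50, 148 | 26, 53, 149 |
| Full trial with true power < 50%, of all feasibility trials | 31% | 28% |

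Simulation with 200,000 runs agrees to within sampling error.

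**5. Sensitivity.**

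- True d = 0.3: 21–23% of feasibility trials show d ≤ 0, and 37–38% lead to power below 50%.
- True d = 0.8: the figures are 1–3% and 20–23%.
- Baseline adjustment at 12 per arm: the half-width is 1.96 × √((2/12)(1 − r²)), in units of the raw SD. This gives 0.69, 0.57 and 0.48 for assumed correlations of 0.5, 0.7 and 0.8. At the most favourable of these, an estimate of 0.5 has limits of 0.02 and 0.98. Since N varies as 1/d², those limits imply sizes differing by (0.98/0.02)² ≈ 2,400-fold.

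**6. The SD, for contrast.** With 22 degrees of freedom its 95% interval runs from 0.77 to 1.42 times the estimate. That is imprecise, but it is bounded and can be allowed for.

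**The case against.** The strongest reply is that the article does not specify a plug-in calculation. It says the results provide data for effect size estimation, plans confidence intervals, and uses the data together with other parameters. It does not rule out an important difference or an allowance for uncertainty, and a condensed article may leave the sizing method to a fuller document. This stands in part: the table in step 4 shows what one natural procedure would do, not what the article commits to. But the article does state where the effect size comes from and what it is for. Planning a confidence interval does not supply a target difference.

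Other points on that side also stand.

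- The 24 analysed children are inferred. The 20% illustrates precision, and outcome analyses are not restricted to completers. Keeping all 30 narrows the interval only to ±0.72.
- A reader might infer that, with many measures and none primary, the sizing outcome will be whichever shows the largest effect. The article contains no such step, and it calls the target-word tasks a key outcome. What remains is only that the outcome for sizing is not formally fixed.
- The abstract's phrase about the power of MAP may be ordinary language for potency, not a claim to estimate statistical power. It is ambiguous, not plainly wrong.
- Nothing here affects this trial's conduct, safety or feasibility estimates, and the later trial will have its own protocol.

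**Conclusion.** The point holds in a limited form. The article plans to use the between-arm effect size from 30 children in sizing the full trial, names no externally justified target difference, and justifies 30 on other grounds. The 95% half-width for d is about 0.72 to 0.80, under 1:1 allocation and no baseline adjustment. Plausible adjustment narrows it, but not enough to set a sample size. With a true d of 0.5 and the point estimate plugged in, 37–42% of such feasibility trials would either show no benefit (9–11%) or lead to a full trial with true power below 50% (28–31%).

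It would go too far to conclude that the article lets the observed effect alone dictate the size, or that this trial should not proceed. The harm is prospective and falls on the later trial, and the repair is one of wording. It should be made, but it is not critical to running this study. Using the trial for SDs, recruitment and retention is sound.

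**What to change.** In the second objective and in the data handling and analysis plan, state the following.

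1. The full trial will be sized on a pre-specified important difference in one named outcome at one time point. The target-word score post-intervention is an obvious candidate; the investigators may prefer another. The difference should be justified independently of this trial's estimate, for example with clinicians and parents.
2. This trial will supply the SD of that outcome, its baseline-to-post correlation, and the recruitment and retention rates. The SD should carry an allowance for its uncertainty. One convention among several is the upper one-sided 80% limit, which at 22 degrees of freedom multiplies the SD by 1.16 and N by 1.16² ≈ 1.35.
3. The MAP–TAU difference will be reported with its 95% confidence interval, for description only.

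Reword the abstract's phrase about estimating power to match. Naming an outcome for sizing does not require a primary outcome for this trial.

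The cost is a few sentences, with no extra children, visits or measures. The full-trial size may come out larger than the observed effect would have suggested.

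### The PI both allocates every child and analyses the data, so the stated blind analysis is not secured

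*Protocol article*

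**What the plan says.** Under Study design, the protocol article states that the minimisation program "will be used by the PI" and that its purpose is "to assign the participants randomly to either the music-assisted (MAP) intervention or treatment as usual (TAU) group using minimisation randomisation". The PI is described as someone "who will have no prior interactions with the participants". The balancing factors are set out as follows: "Gender, developmental stage (IQ ≥ 70 or 50–69) and echolalia (present or absent, as reported by the parents) will be used to balance participants".

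Under Data handling and analysis plan, the article states that "The numerical data will be analysed blind to allocation". The mechanism follows at once: "The blinding will be carried out once the data are collected by generating a new series of participant codes, removing data that could lead to" (the quote stops short; what goes is anything by which a child might be recognised). A different team member carries out that step. The data will go to the PI "and then be analysed by the PI".

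**The concern.** The person described as blind at analysis is the person who assigned each child. New participant codes stop a direct look-up of an individual child. They do not remove the allocator's knowledge of how each arm is made up, and an analyst who wants to know which arm is which needs only to match two groups.

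What is at stake is modest but real. The Baseline and outcome measures section concedes that little blinding is possible, because parents administer the measures after using the intervention methods themselves. A blinded analysis is one of the few safeguards left. No primary outcome is fixed, and the results feed the effect-size and sample-size estimates for the full trial. A report that repeats the blinding statement would claim more protection than the design provides.

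**Working it through.** **The plan's own figure.** The only sample-size calculation is the precision of a 20% drop-out rate with n = 30: 1.96 × √(0.2 × 0.8 / 30) = 0.143, which matches the stated ±14%. The point here does not depend on it, but it confirms that 30 is the working size.

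**Step 1: roles.**

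| Task | Who | Section |
|---|---|---|
| Runs the minimisation | PI | Study design |
| Re-codes participants, removes identifying data | Another team member | Data handling and analysis plan |
| Analyses the numerical data | PI | Data handling and analysis plan |

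The first and third rows name the same person. Neither section says that the PI's access to the allocation list is closed.

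**Step 2: which minimisation factors could be read from the analysed data?**

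- *Gender.* SRS-2 raw scores and gender-normed T scores are both analysed. A raw score and its T score side by side can show which norm was used.
- *IQ band.* The VABS-3 is an outcome and is also the instrument that the exclusion criteria name for IQ. I take it that the same instrument sets the 50–69 / ≥ 70 split.
- *Echolalia.* It is reported by parents for balancing and is not a listed outcome. It is in the file only if it is kept as a baseline variable.

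**Step 3: how often would the coded arms be distinguishable?** Minimisation of 30 children on three binary factors was simulated, with 4,000 trials per setting. The article gives no prevalences and no assignment probability, so these are assumptions: male 50, 75 or 85%; IQ ≥ 70 in 30 or 50%; echolalia in 30 or 50%; probability of the preferred arm 0.8 or 1.0. For someone holding the allocation list, the arms cannot be told apart when their cross-tables are identical.

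| What can be read from the file | Arms identical | Arms distinguishable |
|---|---|---|
| Gender and IQ band (4 cells, 30/4 = 7.5 children per cell on average) | 1.5 to 8.5% | 91.5 to 98.5% |
| All three factors (8 cells, 30/8 = 3.75 per cell) | 0 to 0.7% | 99.3% or more |
| Arm size only | 54.5 to 85.7% | 14.3 to 45.5% |

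The right-hand column is 100% minus the middle one. A separate simulation with prevalences of 80, 40 and 50% and assignment probabilities of 1.0, 0.8 and 0.7 gave identical 8-cell tables in 0.25, 0.15 and 0.08% of trials, in line with the second row.

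The third row shows what thorough stripping would achieve: the arms are then alike in about 55 to 86% of trials. But hiding gender and IQ band this way would mean withholding from the analyst scores that the article lists for analysis.

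**Step 4: app data.** The app belongs to the MAP intervention, and usage is reviewed for MAP dyads. These data reveal the arm only if they can be linked to the outcome file.

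**The case against.** A reader might infer that the blinding claim is simply false, or that the analysis will be biased. The article supports neither.

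- **There is a safeguard.** A second team member re-codes the children and removes identifying data. If that step masks the arm labels and takes out the factor-bearing scores, or if the PI no longer has the list, a masked analysis is possible. A condensed article may leave to a fuller document which variables are removed and how arms are labelled, so that silence is not a fault in itself. This stands, and it is why the claim is unsecured rather than refuted.
- **The figures are conditional.** Over 99% needs all three factors in the file. Every percentage needs the analyst to hold the list and compare tables deliberately, and rests on assumed prevalences. This stands too.
- **The app data may sit apart.** The usage review is a separate feasibility question, and nothing says that it shares a file with the outcomes. This stands.
- **The stakes are limited.** The analysis is descriptive, no covariate-adjusted model is stated, and the choice of mean or median follows a stated rule. The article is candid about limited blinding and promises open data and code. This lowers the seriousness of the point but does not remove the conflict of roles.
- **The PI was chosen as allocator for a reason.** Having no prior contact with participants protects against selection bias. Any new allocator must meet the same condition. But that property concerns the moment of allocation and does nothing for blinding at analysis.

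**Conclusion.** The point holds in this form: the article assigns allocation and blind analysis to the same person, and later re-coding by a colleague is the only stated barrier between them. With 30 children, and if gender and IQ band can be read from the SRS-2 and VABS-3 scores, the holder of the allocation list could match the coded arms in about 91 to 98% of trials. If echolalia is also present, the figure is over 99%. These results assume the prevalences and assignment probabilities listed above, continued access to the list, and all 30 children in the file. They measure the opportunity to unmask, not its occurrence. The correction should be made, but it does not threaten the trial: no sample size, error rate or stated precision changes.

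**What to change.** Separate the two roles within the existing team. A member with no analysis role and no prior interaction with participants runs the minimisation and keeps the allocation list. The PI receives arms labelled A and B, and the MAP app-usage data are kept separate until the analysis code is frozen.

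If the PI has already begun allocating, there are two alternatives. One is to freeze the R script on dummy arm labels before outcome data are released. The other is to replace the blinding claim with a plain statement that the analyst performed the allocation.

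The cost is a small reassignment of duties and a sentence each under Study design and Data handling and analysis plan. The one constraint is that the new allocator must meet the no-prior-contact condition; the article does not say whether the member who re-codes the data does.
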